## Abstract

**Background:**

Depression is common among women during perinatal period and is associated with long-term adverse consequences for the mother and infant. In Nigeria, as in many other low- and-middle-income countries (LMIC), perinatal depression usually goes unrecognized and untreated. The aim of EXPONATE is to test the effectiveness and cost-effectiveness of an intervention package for perinatal depression delivered by community midwives in primary maternal care in which physician support and enhanced patient compliance are implemented using mobile phones.

**Methods/Study design:**

A pragmatic two-arm parallel cluster randomized controlled trial was designed. The units of allocation are the primary maternal care clinics. Thirty eligible and consenting clinics were randomized but, due to problems with logistics, 29 eventually participated. Consenting pregnant women with a gestational age between 16 and 28 weeks who screened positive on the Edinburgh Postnatal Depression Scale (EPDS score ≥12), absent psychosis or bipolar disorder, and not actively suicidal were recruited into the trial (N = 686). Midwives in the intervention arm were trained to deliver psychoeducation, problem solving treatment, and parenting skills. Eight weekly sessions were delivered following entry into the study. Further sessions during pregnancy and 6 weeks following childbirth were determined by level of depressive symptoms. Clinical support and supervision, delivered mainly by mobile phone, were provided by general physicians and psychiatrists. Automated text and voice messages, also delivered by mobile phones, were used to facilitate patient compliance with clinic appointments and ‘homework’ tasks. Patients in the control arm received care as usual enhanced by further training of the providers in that arm in the recognition and standard treatment of depression. Assessments are undertaken at baseline, 2 months following recruitment into the study and 3, 6, 9 and 12 months after childbirth. The primary outcome is recovery from depression (EPDS < 6) at 6 months. Secondary outcomes include measures of disability, parenting skills, maternal attitudes, health care utilization as well as infant physical and cognitive development comprehensively assessed using the Bayley’s Scales.

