### Setting

The study was conducted in Oyo State, Nigeria. The state has 33 local government areas (LGA). All 137 maternal and child care clinics (MCCs) in nine LGAs selected for the study (five rural and four urban) were assessed for eligibility to participate. MCCs are the main source of care for most low-income perinatal women and are therefore the appropriate place to test an intervention package that is designed to make a major impact on the delivery of care to this population. Maternal and child health services in these clinics are largely delivered by non-physician primary care providers and midwives, who have been trained as nurses, community health officers and community health extension workers. Each of these categories of providers has a minimum of 2–3 years post-secondary education and are certified by their respective boards. Supervision for all the clinics in each LGA is provided by one general practitioner employed by the government and designated as the Primary Health Care Coordinator for the Local Government.

We used both urban and rural areas in order to capture the diversity of socioeconomic profile of the country and because access to medical treatment differs substantially between these two types of setting, thus making the demonstration of the utility of our program potentially more generalizable.

Eligible clinics were those that offer full maternal and child health services (*n* = 49). The study procedures were described to the supervising physicians in each of the LGAs and to the facility managers in each of the eligible clinics. Only clinics providing explicit consent to participate were randomized into the trial. Of the 30 that did so, one was excluded because the staffing profile was too thin to permit for effective participation, thus leaving 29 included in the trial.

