### Randomization

Eligible and consenting maternal care clinics were stratified by local government area and allocated to intervention or control arm using a computer-generated random number sequence. Allocation was conducted by one of the authors ([name]) using anonymous codes for clinics and LGAs provided by other members of the research team, in order to avoid any risk of selection bias.

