### Sample size

Experience from our previous studies in primary health care (PHC) as well as from the control arm of a Pakistani trial among women with perinatal depression suggests a recovery rate of about 45 % for major depression with no active treatment and about 75 % with treatment [29]. In a Chilean study of postnatal women with depression, using a 3-point reduction in baseline score of the depression assessment tool, remission rate was 57 % with no active treatment and 73 % with active treatment [28]. For our sample size estimation, we sought to detect an absolute difference of 15 percentage points (40 % recovery in control and 55 % in intervention groups respectively) at 6 months, a difference that we think is both plausible for this type of intervention and would promote changes in practice. In our pilot study among antenatal women, we observed an intra-cluster correlation coefficient (ICC) of 0.026 for EPDS scores. In our pilot study among general adults with depression, we were able to collect primary outcome at 6 months from 87.8 % of the participants. We expect a higher follow-up rate among perinatal women who generally are less likely to move. However, we will use a conservative 6-month follow-up rate of 85 % for our estimate. We also assume a 7 % infant death rate within the period. The uninflated sample size requires 186 per arm for analysis to detect a difference of 55 % vs 40 % (equivalent odds ratio = 1.8) with 80 % power at the two-sided 5 % alpha level. We originally aimed to recruit 50 individuals per MCC. With 43 individuals per cluster available for the primary analysis and an ICC of 0.026, the design effect is 2.09 giving a total number required for analysis of 778. We therefore aimed to recruit a total of 916 individuals from a total of 18 MCCs. As participant recruitment was slower than anticipated, in January 2014 we recruited and randomised a further 11 MCCs, giving a total of 29 in the study. Participant recruitment took place between July 2013 and October 2014. Outcome assessments are still ongoing and will continue till one year post-delivery assessment is concluded for the last recruited participant.

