### Data analysis

A full statistical analysis plan will be developed before any data are analyzed. The analysis and presentation of the trial will be in accordance with CONSORT guidelines for cluster randomized trials [46, 47]. The primary approach for comparative analyses will be to analyze participants as randomized without imputation of missing data, and with due emphasis placed on confidence intervals for the between-arm comparisons. We will use descriptive statistics to assess balance between the trial arms at baseline for both clinic and individual participant characteristics. In order to take appropriate account of the hierarchical nature of the data, we will use multivariable mixed effects regression models to estimate recovery from depression at 6 months for intervention group versus control, adjusting for baseline depression and LGA as a stratification variable. In a secondary analysis, we will further adjust for any variables that were imbalanced between trial arms at baseline. These analyses will be repeated for secondary outcomes. We will conduct sensitivity analyses to assess the potential effect of missing data, and will investigate the effect of adherence with the intervention. We will investigate whether between-group differences vary over time using data from all follow-up visits in repeated measures analyses.

We will investigate whether there is any differential effect of the intervention according to baseline symptom severity (EPDS score <16, ≥16) by including appropriate interaction terms in the primary regression model. Since the trial is powered to detect overall differences between groups rather than interactions of this kind, the results will be interpreted with due caution.

Data analysis will be conducted once all follow-up is complete. There are no planned interim analyses.

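### Clinics were randomised in at least two rounds, but the primary model adjusts only for baseline depression and LGA and leaves out randomisation round

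*Protocol article*

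**What the plan says.** - **Abstract, Methods/Study design:** "Thirty eligible and consenting clinics were randomized but, due to problems with logistics, 29 eventually participated".
- **Setting:** "Only clinics providing explicit consent to participate were randomized into the trial". The next sentence says: "Of the 30 that did so, one was excluded because the staffing profile was too thin to permit for effective participation". This leaves 29.
- **Randomization:** "Eligible and consenting maternal care clinics were stratified by local government area and allocated to intervention or control arm". The section gives one method and does not mention rounds.
- **Sample size:** the plan was "We therefore aimed to recruit a total of 916 individuals from a total of 18 MCCs". Recruitment was slow, so "in January 2014 we recruited and randomised a further 11 MCCs, giving a total of 29 in the study". Participants were recruited from July 2013 to October 2014.
- **Data analysis:** "The primary approach for comparative analyses will be to analyze participants as randomized without imputation of missing data". The primary model is a mixed effects regression adjusted for baseline depression and for LGA, the latter expressly because it was a stratification variable. A secondary analysis adds variables found to be imbalanced at baseline.

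**The concern.** The plan includes LGA because allocation was stratified by it. The same reasoning covers round. The January 2014 clinics were allocated separately, about half a year into recruitment, and could enrol women only in the later part of the window. If recovery differs between the two sets of clinics, for example through season, staff experience or outcome assessors' practice, and the arms hold different shares of each set, part of that difference enters the treatment comparison. The analysis would also ignore a restriction that the allocation imposed, which the plan avoids for LGA.

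A second, smaller matter is the cluster flow. The abstract reads as if one clinic was lost after allocation. In Setting, the words about the 30 can refer to consenting or to being randomised, so the timing of the exclusion is open. The article gives neither that clinic's arm, LGA or round, nor whether it had enrolled anyone. If staffing was judged too thin once allocation was known, the judgement might not have been neutral between arms, because the intervention asks more of staff than the control arm does.

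**Working it through.** **1. The plan's own figures.** The sample-size chain reproduces.
- 40% versus 55%, 80% power, two-sided 5%: 173 per arm without continuity correction and 186 with it. The plan gives 186.
- Design effect: 1 + (43 − 1) × 0.026 = 2.092.
- Number for analysis: 2 × 186 × 2.092 = 778.
- Number to recruit: 778 / 0.85 = 916.
- Clinics: 18 + 11 = 29, the number given as in the study.

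**2. Recruitment windows.** July 2013 to October 2014, counting both end months, is at most 16 months. January to October 2014 is at most 10. First-round clinics may have gone on recruiting in 2014, so round marks the clinic set and only partly the calendar period.

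**3. How far round could be tied to arm.** The splits are not reported, so these are illustrations. They assume that the 29 − 11 = 18 initial clinics split 9:9 and that clinics weigh equally.

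| Split of the 11 | Later-round share, larger arm | Later-round share, smaller arm | Difference |
|---|---|---|---|
| 6:5 | 6/15 = 40.0% | 5/14 = 35.7% | 4.3 points |
| 7:4 | 7/16 = 43.8% | 4/13 = 30.8% | 13.0 points |

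The shift in an unadjusted risk difference is the difference in shares times the difference in recovery between rounds. As a deliberately large value, take that second difference as 15 points, the effect the trial is designed to detect.
- 6:5: (0.4000 − 0.3571) × 15 = 0.64 points.
- 7:4: (0.4375 − 0.3077) × 15 = 1.95 points.

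These figures ignore the planned LGA adjustment, which would absorb part or all of the shift if the rounds came from different LGAs.

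**4. Cost.** With at most nine LGAs as fixed effects, the clinic-level residual degrees of freedom are 29 − 1 (intercept) − 1 (arm) − 8 (LGA) = 19. Adding round leaves 18.

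**5. Can the clinic counts be reconciled?** In Sample size, 18 is a planned number and 29 is the number in the study. Neither is a count of clinics randomised. Two histories fit most of the text:
- 19 + 11 = 30 randomised, one lost afterwards, 29 in the study. This fits the abstract.
- 30 consented, one excluded before allocation, 18 + 11 = 29 randomised. This fits one reading of Setting but makes the abstract's wording inaccurate.

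The article does not say which occurred.

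**6. Effect of the count on power.** With 686 × 0.85 = 583 women analysed, equal clusters and ICC 0.026:
- 29 clinics: 583/29 = 20.11 per clinic, design effect 1.497, effective 194.8 per arm, power 84.5% (81.9% with continuity correction).
- 30 clinics: 583/30 = 19.44 per clinic, design effect 1.479, effective 197.1 per arm, power 84.9% (82.4%).

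The difference is about half a point.

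**The case against.** The strongest reply is that covariate detail belongs in the statistical analysis plan, which the article promises before any data are analysed. The Randomization section states a method that may have been used in both rounds, and the second round is openly reported. A 6:5 split is nearly balanced, and no confounding has been shown. If the added clinics came from other LGAs, the LGA terms already carry round.

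Much of this stands. Confounding is possible but not demonstrated, and the overlap of round with LGA is unknown. But the article does not leave the adjustment set open: it names it, and gives stratification as the reason for LGA, after the second randomisation had taken place. The planned secondary adjustment is no substitute, because it depends on observed imbalance and lies outside the primary analysis.

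On the clinic flow, a reader might infer more than the text supports:
- **That 18 + 11 = 29 contradicts 30 randomised.** It need not, because 18 was a plan and 29 counts clinics in the study.
- **That the two reasons for the loss conflict.** Thin staffing can be described as a logistics problem.
- **That about 24 women (686/29 = 23.7) were dropped, breaching analysis as randomised.** That figure is the mean size of the participating clinics. Nothing says the lost clinic enrolled anyone, and the commitment concerns participants.

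**Conclusion.** The point holds in a limited form. Randomisation took place in at least two rounds, and the stated primary model accounts for LGA but not for round. The omission should be corrected because the analysis should follow the allocation, not because bias has been shown. Under the illustrated splits the shift is about 0.6 to 1.9 percentage points against a target of 15, and only if recovery differs between rounds by as much as 15 points. These values rest on an assumed 9:9 initial split, equal clinic weights and no absorption by LGA.

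The account of the thirtieth clinic is unclear but not strictly contradictory. If it left after allocation, the randomised set of clusters was altered and this must be reported. The documents do not show that enrolled women are missing from the analysis or that the loss depended on arm. Power is practically unaffected.

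**What to change.** **Primary model.** In Data analysis, and in the analysis plan still to be written, add randomisation round (initial set versus January 2014) as a fixed covariate alongside baseline depression and LGA. Carry it into the secondary-outcome models, which repeat the primary one. Specify in advance that the term is dropped if no LGA contains clinics from both rounds, since LGA fixed effects then determine round. The cost is one sentence and 1 degree of freedom. The gain is small if round largely coincides with LGA.

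**Clarification.** Reconcile the abstract, Setting, Randomization and Sample size sections. Give the number of clinics randomised per round and per arm. State whether the excluded clinic left before or after allocation, its arm if allocated, and whether it had enrolled anyone. If it left after allocation, say that 29 of 30 randomised clinics are analysed and show the loss in the cluster flow that the promised CONSORT reporting requires. This costs wording only.

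A sensitivity analysis that removes the lost clinic's whole LGA is not needed: it would discard further randomised clinics to address a loss of participants that has not been shown.

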**Discussion:**

To the best of our knowledge, this is the largest randomized controlled trial of an intervention package delivered by community midwives in sub-Saharan Africa.

**Trial registration:**

Trial is registered with the ISRTCN registry at isrtcn.com; Trial number ISRCTN60041127. Date of registration is 15/05/2013.

## Background

Depression is one of the most common disorders in adult life with adverse consequences for health and social wellbeing [1]. More than 13 % of the global burden of disease is due to neuropsychiatric disorders, with depression being the leading cause of the burden [2, 3]. Epidemiological studies conducted in Nigeria find 10–20 % of consecutive attendees in primary care have depression [4, 5]. Depression is particularly common amongst women of child bearing age. One systematic review estimated the point prevalence of major and minor depression to be between 8.5 and 11 % during pregnancy and between 9.7 and 12.9 % postnatally [6]. In Nigeria, rates of up to 10–30 % have been reported amongst perinatal women [7–11].

Perinatal depression, defined as non-psychotic depressive episode often beginning during pregnancy or the postnatal period, is a substantial public health problem, not only because it is common but also because it is associated with long term adverse consequences on infant development and mother-child interactions [12]. Maternal depression is a risk factor for pre-term birth and low birth weight, infant under-nutrition and stunting as well as higher rates of diarrhoeal diseases [13–17]. Infants of depressed mothers also show poorer infant development as assessed using standardized measures, poorer interpersonal functioning, insecure attachment and elevated rates of emotional and behavioural problems [16, 18–20].

Worldwide, only a minority of depressed persons get the care they need [21]. Depressed women, especially those in the perinatal period, are particularly less likely to have their mental health needs met. It has been estimated that less than 50 % of cases of postnatal depression are detected by primary health care professionals in routine clinical practice [22]. This estimate was made for settings with much better resourced health care systems than are found in low and middle income countries (LMIC). It is very likely that a much smaller proportion of cases are identified and treated in Nigeria and other LMIC. Hence there is a huge level of unmet need for service in LMIC. For example, a previous study in Nigeria found that about four out of five persons with severe mental disorders, particularly depression, had received no treatment in the previous year and that, among those who did, only about 10 % had received what could be described as minimally adequate treatment [21]. The extent of the treatment gaps in LMIC reflects the extreme paucity of resources, both human and material. In sub-Saharan Africa, there is less than one psychiatrist to one million population and the few available specialists are based in urban areas [23]. Less than 2 % of the national budget goes to health and, within this, mental health service is hardly featured [23]. In addressing these gaps, it is now commonly agreed that the most effective way to bring health care to more people in need is through the integration of mental health services into routine primary care and maternal care so that non-physician health care providers at primary health clinics or dispensary level deliver the bulk of essential mental health service under the supervision and support of physicians or psychiatric nurses at district/local government level, who are themselves supported by more highly trained mental health specialists at regional/state levels [24].

Evidence from systematic reviews shows that perinatal depression can, in most instances, be effectively managed with psychological treatments [25, 26]. Even though much of this evidence has come from studies in high-income countries, previous studies in some LMIC have also shown that psychological interventions can be delivered by non-specialist health workers, such as community health workers (CHWs), including community midwives (CMWs) [27–29]. The results of these studies suggest that there is a need for training of the CMWs to deliver the intervention in a way that is sustainable within their day-to-day practice and that close supervision and support are available to these providers.

There is now considerable evidence in support of stepped care approaches to expanding mental health services [30]. In this model, non-physician primary care providers deliver the bulk of essential mental health service under the supervision and support of physicians and of more highly trained mental health specialists, if these are available. The essential ingredients to scale up mental health services to perinatal women are therefore generally agreed upon. However, considerable challenges remain to translate this knowledge into practice in diverse settings. This is especially so in regard to building an integrated treatment system out of the available resources in LMIC.

## Methods/Design

### Aim of the study

The primary aim of this study is to test the effectiveness and cost-effectiveness of a stepped care intervention package for perinatal depression delivered by community midwives in primary maternal care, supported by physicians and mental health specialists through the use of mobile phones, compared to usual care in a randomized controlled trial.

The primary hypothesis is that the intervention package will be more effective at alleviating depression at 6 months after childbirth compared to care as usual. The secondary hypotheses are that: 1) the intervention package will be more cost-effective; 2) will lead to better infant outcomes (in regard to cognition and growth) at 12 months; 3) will be associated with better parental skills of mothers; and 4) will lead to less experience of perceived stigma.

### Design

This study was a two-arm parallel cluster randomized controlled trial comparing an intervention package for maternal depression consisting mainly of psychological interventions (psychoeducation, problem solving treatment and parenting skills) with care as usual. The unit of randomization was the primary maternal care clinic; interventions and outcome measures were however administered on individual participants. As the intervention was designed to be delivered by clinic staff, the cluster randomized design was chosen in order to reduce the potential risk of contamination within clinics.

